## Abstract

**Introduction:**

Angina with no obstructive coronary artery disease (ANOCA) is a common syndrome with unmet clinical needs. Microvascular and vasospastic angina are relevant but may not be diagnosed without measuring coronary vascular function. The relationship between cardiovascular magnetic resonance (CMR)-derived myocardial blood flow (MBF) and reference invasive coronary function tests is uncertain. We hypothesise that multiparametric CMR assessment will be clinically useful in the ANOCA diagnostic pathway.

**Methods/analysis:**

The Stratified Medical Therapy Using Invasive Coronary Function Testing In Angina (CorMicA) trial is a prospective, blinded, randomised, sham-controlled study comparing two management approaches in patients with ANOCA. We aim to recruit consecutive patients with stable angina undergoing elective invasive coronary angiography. Eligible patients with ANOCA (n=150) will be randomised to invasive coronary artery function-guided diagnosis and treatment (intervention group) or not (control group). Based on these test results, patients will be stratified into disease endotypes: microvascular angina, vasospastic angina, mixed microvascular/vasospastic angina, obstructive epicardial coronary artery disease and non-cardiac chest pain. After randomisation in CorMicA, subjects will be invited to participate in the Coronary Microvascular Angina Cardiac Magnetic Resonance Imaging (CorCMR) substudy. Patients will undergo multiparametric CMR and have assessments of MBF (using a novel pixel-wise fully quantitative method), left ventricular function and mass, and tissue characterisation (T1 mapping and late gadolinium enhancement imaging). Abnormalities of myocardial perfusion and associations between MBF and invasive coronary artery function tests will be assessed. The CorCMR substudy represents the largest cohort of ANOCA patients with paired multiparametric CMR and comprehensive invasive coronary vascular function tests.

**Ethics/dissemination:**

The CorMicA trial and CorCMR substudy have UK REC approval (ref.16/WS/0192).

**Trial registration number:**

NCT03193294.

Key questionsWhat is already known about this subject?Angina with no obstructive coronary artery disease (ANOCA) is a common syndrome with unmet clinical needs.A significant proportion of these patients may suffer from microvascular and vasospastic angina.Diagnosis in this patients may be challending, are there are uncertain associations between the results of reference invasive diagnostic tests and the non-invasive ischaemia test results.What does this study add?Novel CMR methods for measuring myocardial blood flow have not been validated in patients with ANOCA and underlying microvascular and vasospastic angina.The CorCMR substudy represents the largest cohort of ANOCA patients with paired multiparametric CMR and comprehensive invasive coronary vascular function tests. CorCMR will provide information on the diagnostic value of quantitative pixel-wise mapping of myocardial perfusion in patients with ANOCA.How might this impact on clinical practice?In contrast to the reference standard invasive tests of coronary artery function, non-invasive imaging is safer and more acceptable to patients.The CorCMR sub-study presents a unique opportunity to assess and validate the diagnostic accuracy of fully-quantitative stress perfusion CMR in patients with ANOCA and comprehensive invasive coronary artery function testing.

## Introduction

### Angina and stable coronary syndromes (SCSs)

Ischaemic heart disease is the leading cause of mortality standardised by age and sex.^1^ In clinical practice, the diagnostic management of patients with angina pectoris focuses on the detection of obstructive epicardial coronary artery disease (CAD).^2^ In this stenosis-centred concept of myocardial ischaemia, angina is synonymous with obstructive CAD.^3^ There are well established treatment options for patients with epicardial CAD, namely optimal medical therapy and myocardial revascularisation by either percutaneous coronary intervention or coronary artery bypass grafting.^3^ However, the paradigm of angina pectoris resulting from obstructive epicardial CAD fails to account for the approximately one-third of patients who suffer from angina in whom obstructive CAD is excluded.^4^

Patients with angina and no obstructive coronary artery disease (ANOCA) present a diagnostic conundrum.^5^ The management of these patients is varied, and most patients fail to have a diagnosis made for the cause of their symptoms, receive no further diagnostic work-up, and have no therapeutic intervention. The underlying aetiology of chest pain symptoms and a ‘negative’ coronary angiogram is heterogeneous. However, a significant number of patients may have a disorder of coronary vascular function due to abnormal microvascular resistance or vasodilator capacity (coronary microvascular dysfunction (CMD)) or abnormal endothelial function (vasospastic disease).

The underlying pathogenesis in patients with ANOCA is unclear, as specific disease endotypes are not routinely tested for. CMD may result from coronary structural abnormalities, whereby decreased capillary luminal size and number result in increased microvascular resistance to myocardial blood flow (MBF) and reduced vasodilatory capacity.^6^ Functional abnormalities of the coronary epicardial vessels and microvasculature may result in either abnormal vasoconstriction or impaired vasodilatation, and these abnormalities may be secondary to either endothelium-dependent or endothelium-independent mechanisms.^7^

Abnormalities of coronary vascular function portend a worse prognosis in patients with both obstructive epicardial CAD and ANOCA.^8–12^ Therapeutic interventions are lacking in patients with ANOCA, and historical therapeutic studies have been performed in heterogeneous patient cohorts due to a lack of diagnostic tests to appropriately define endotypes of disease.^13–15^ There is a missing link between the use of diagnostic tests of coronary artery function, therapeutic agents with proven efficacy and health outcomes of patients with angina secondary to disorders of coronary vascular function. The term stable coronary
syndrome (SCS) has been proposed to increase physician awareness of these conditions.^5^ CMD and vasospastic disease may result in ANOCA and myocardial ischaemia, and are recognised as a condition of unmet clinical need.^16^ The Coronary Vasomotion Disorders International Study Group (COVADIS) working group have proposed diagnostic criteria for disease endotypes in patients with ANOCA.^17^ COVADIS recommend a comprehensive testing strategy incorporating tests of coronary pressure, flow, resistance and endothelial function, in addition to the assessment of objective evidence of myocardial ischaemia.^17^

### Diagnostic testing in patients with ANOCA

Diagnosis of coronary microvascular and vasomotor dysfunction is challenging due to the heterogeneity of underlying disease mechanisms, the potentially patchy distribution of disease throughout the myocardium, and limited spatial resolution of existing diagnostic tests.^18 19^ There is no available in vivo technique for imaging the coronary microcirculation, and anatomical tests are fundamentally limited by their spatial resolution and the small size of the coronary microvasculature. Therefore, the diagnosis of microvascular angina and vasospastic angina is predominantly made with functional tests.

There is no accepted guideline-directed diagnostic algorithm for coronary vascular dysfunction in routine clinical practice.^17 20^ Invasive coronary angiography combined with adjunctive tests of coronary artery function represents the reference diagnostic approach for disorders of coronary vascular function. In contrast, non-invasive imaging involves less discomfort for patients, is safer than invasive procedures and is generally less expensive and more widely available. Recent developments with cardiovascular magnetic resonance (CMR) imaging now enable measurement of MBF with high spatial and temporal resolution.^21^ In addition, CMR permits the reference standard non-invasive assessment of left ventricular (LV) function and myocardial tissue characterisation.^22^

### Non-invasive ischaemia testing in ANOCA

The available non-invasive ischaemia tests were all validated for the detection of obstructive epicardial CAD. There has been a low yield of inducible myocardial ischaemia in ANOCA patients with traditional non-invasive ischaemia tests (e.g. exercise ECG testing, myocardial perfusion scintigraphy and stress echocardiography).^23^ However, non-invasive methods (namely stress perfusion positron emission tomography (PET) and CMR which image earlier in the ischaemic cascade and have greater spatial resolution) may provide new insights into the burden of myocardial ischaemia in patients with ANOCA. PET is the most studied modality for the assessment of myocardial perfusion and is considered to provide the reference standard assessment of MBF, but in real-world clinical practice, availability is limited due to cost. Conversely, CMR is more widely available and use is increasing.^24 25^

Coronary microvascular disease may be revealed by a deficit in MBF during stress CMR. The spatial distribution of this abnormality typically involves the subendocardium, which is the location of the microvascular plexus.^26^ In contrast, vasospastic angina occurs due to spontaneous spasm of the epicardial and microvascular vasculature. Vasospastic angina may not be detected by conventional stress testing that routinely use adenosine (an endothelial-independent vasodilator). The available data are conflicting on the role of perfusion CMR in patients with ANOCA.^26–28^ In contrast to qualitative analysis, semiquantitative perfusion methods have been investigated, and reduced myocardial perfusion reserve index (MPRi) has been found in patients with ANOCA.^29^ The incremental diagnostic value of fully quantitative perfusion CMR in patients with ANOCA is unknown.

### Associations between invasive and non-invasive diagnostic tests in patients with ANOCA

There are uncertain associations between the results of invasive diagnostic tests and the non-invasive ischaemia test results in patients with ANOCA. There is no accepted objective diagnostic threshold for the diagnosis of coronary vascular dysfunction (either abnormal myocardial flow or microvascular resistance), with either PET or perfusion CMR. Recent studies have investigated the relationships between invasive tests of coronary artery function and semiquantitative perfusion CMR analysis.^30 31^ Importantly, these patients have not undergone comprehensive coronary vascular function testing and in general moderate correlations were demonstrated (MPRi and index of microcirculatory resistance (IMR): r=−0.67; MPRi and coronary flow reserve (CFR): r=0.41).^30^

### The Stratified Medical Therapy Using Invasive Coronary Function Testing In Angina (CorMicA) trial

The Stratified Medical Therapy Using Invasive Coronary Function Testing In Angina (CorMicA) clinical trial is a proof-of-concept, prospective, blinded, randomised, sham-controlled study comparing two management approaches to the clinical problem of patients with ANOCA.^32^ CorMicA tests the hypothesis that stratified medicine guided by invasive coronary artery function testing (interventional diagnostic procedure (IDP)) in patients with ANOCA will facilitate diagnosis of the underlying disease endotype, direct therapeutic interventions aligned to the endotype and result in improved angina and well-being.^32^ Patients undergoing elective invasive coronary angiography for investigation of angina at two UK centres will be screened. Eligible patients with ANOCA (n=150) will be immediately randomised 1:1 to either coronary vascular function-guided diagnosis and treatment (intervention group/IDP disclosed) or not (control group/IDP sham procedure, results not disclosed) (figure 1).

**Figure 1 F1:**
[figure not shown]
CorCMR substudy flow diagram. ANOCA, angina with no obstructive coronary artery disease; CMR, cardiovascular magnetic resonance; CorCMR, Coronary Microvascular Angina Cardiac MRI; CorMicA, coronary microvascular angina.

The IDP consists of coronary artery function testing using a dual pressure-sensitive and temperature-sensitive guidewire and adenosine followed by intracoronary acetylcholine provocation testing. Assessment of microvascular resistance (IMR), microvascular vasodilatory capacity (resistance reserve ratio (RRR)), epicardial and microvascular vasodilatory capacity (CFR), endothelial function (acetylcholine provocation testing) and epicardial CAD (fractional flow reserve (FFR)) will be performed. Following these invasive tests of coronary artery function, patients will be classified into the following ANOCA disease endotypes (table 1): (1) microvascular angina; (2) vasospastic angina; (3) mixed microvascular angina and vasospastic angina; (4) obstructive epicardial CAD; and (5) non-cardiac chest pain. The disease endotypes are aligned with the COVADIS working group definitions.^17^

**Table 1 T1:** Definitions of ANOCA disease endotypes

Disease endotype	Mechanism	Invasive diagnostic test
Microvascular angina	↑ Microvascular resistance	IMR ≥25
	↓ Coronary vasorelaxation	CFR <2.0
	↓ Microvascular vasodilator capacity	RRR <2.0
	Microvascular spasm	ACh testing: angina, ischaemic ST segment deviation, epicardial coronary vasoconstriction <90%.
Vasospastic angina	Epicardial spasm	ACh testing: angina, ischaemic ST segment deviation, >90% epicardial coronary vasoconstriction.
Mixed microvascular and vasospastic angina	CMD and epicardial vasospasm	Epicardial vasospasm and either ↑ microvascular resistance, ↓ coronary vasorelaxation or ↓ microvascular vasodilator capacity.
Obstructive epicardial CAD	Epicardial stenosis	>50% lesion by diameter stenosis in epicardial artery >2.5 mm or FFR ≤0.80.
Non-cardiac pain	Nil	Exclusion of epicardial (FFR >0.8), microvascular (CFR >2.0, IMR <25, RRR >2.0) vasospasm (normal ACh response).

ACh, acetylcholine; ANOCA, angina with no obstructive coronary artery disease; CAD, coronary artery disease; CFR, coronary flow reserve; CMD, coronary microvascular dysfunction; FFR, fractional flow reserve; IMR, index of microcirculatory resistance; RRR, relative resistance ratio.

Patients in the control group will receive standard care based on the interpretation of the invasive coronary angiogram alone. Patients in the intervention group will have care based on the disease endotypes disclosed by invasive tests of artery function, and pharmacotherapy linked to the underlying disease endotype will be commenced.^32^ In each case, the diagnosis (endotype) will be assessed by the attending cardiologist before and after the coronary angiogram. In the intervention group, the diagnosis is re-evaluated after disclosure of the coronary function test results at the end of the invasive procedure. The primary outcome is the mean difference in the within-subject change in Seattle Angina Questionnaire score between the groups at 6 months from baseline. A prespecified substudy of the CorMicA trial investigated the frequency of peripheral microvascular dysfunction in patients with ANOCA.^33^

### Coronary Microvascular Angina Cardiac Magnetic Resonance Imaging (CorCMR) sub-study

Novel CMR methods for measuring MBF have not been validated in patients with ANOCA and underlying microvascular and vasospastic angina. The CorCMR substudy of the CorMicA clinical trial presents a unique opportunity to assess and validate the diagnostic accuracy of fully quantitative stress perfusion CMR in patients with ANOCA and comprehensive invasive coronary artery function testing.

### Hypothesis

We hypothesise that abnormal myocardial perfusion, as revealed by a novel fully quantitative pixel-wise CMR perfusion sequence, will be prevalent in a contemporary UK cohort of patients presenting with ANOCA and that multiparametric CMR imaging will be clinically useful in the diagnostic pathway of patients with ANOCA.

### Aims

We aim to assess the diagnostic validity of quantitative stress perfusion CMR in patients with ANOCA and specific disease endotypes of coronary vascular dysfunction. Our specific aims are to assess:

The proportion of ANOCA patients with abnormal myocardial perfusion. There is no accepted threshold for abnormal MPR. Thresholds for reduced CFR of 1.5–2.6 have been described, however <2.0 is commonly used.^10 34–38^ We will therefore assess the concordance of patient classification using this MPR <2.0 threshold against endotypes determined by invasive testing. Second, we will assess the MPR value with the highest area under the curve (AUC) for classification of microvascular angina based on the invasive tests (reference classification). Third, we will assess the proportion of ANOCA endotypes with other abnormal perfusion metrics (reduced stress MBF, abnormal endocardial:epicardial MBF ratio and abnormal myocardial dyssynchrony index).^39^
The diagnostic accuracy of the perfusion CMR metrics for abnormal invasive tests of coronary artery function (IMR >25, CFR <2.0 and RRR <2.0) and the associations between specific disease endotypes and myocardial perfusion in patients with ANOCA. We also aim to assess the correlation between abnormal CMR-derived perfusion and invasive tests of coronary artery function, of qualitative versus quantitative perfusion methods.The proportion of patients with ANOCA and abnormal myocardial tissue characterisation derived from CMR (as revealed by T1 parametric mapping and late gadolinium enhancement (LGE) imaging) and its association with abnormal myocardial perfusion.The associations between baseline patient characteristics and abnormal myocardial perfusion.The proportion of patients with a change in diagnosis based on quantitative CMR findings, as compared with the initial diagnosis by the attending cardiologist based on the coronary angiogram.

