### Participants

Consecutive outpatients undergoing clinically indicated elective diagnostic angiography for investigation of suspected angina will be screened and invited to participate in the CorMicA trial. Informed consent is obtained before the invasive coronary angiogram. A minimum of 400 consecutive patients undergoing elective invasive coronary angiography is expected to be screened to enrol 150 subjects with ANOCA within 24 months. Consenting patients who are not randomised (e.g. demonstrated to have obstructive epicardial disease or logistical reasons) will enter a registry. Only patients randomised in the CorMicA trial (both in the intervention and control groups) are eligible to participate in the CorCMR substudy.

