### Primary and secondary outcomes

#### Primary outcome

Abnormal myocardial perfusion reserve (global MPR <2.0).

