#### Sample size calculation

The primary outcome is the proportion of patients with an MPR<2.0. The proportion of patients with microvascular angina defined by invasive endotyping will be assessed. We will further assess the MPR ratio with the highest AUC for microvascular angina classified invasively.

Considering the correlation between CFR measured invasively and MPR measured non-invasively within the common territory of a major epicardial coronary artery, then a sample size of 110 subjects would enable a minimum clinically significant correlation of 0.3 to be detected with 90% power at a 5% significance level. If only 60 subjects have available data, then 80% power would be available to detect a correlation of 0.37 at the 5% level.

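### The rule for the data-derived MPR cut-off is loosely worded, and accuracy quoted at that cut-off from the one cohort described would be about 3 to 7 points optimistic unless corrected

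*Protocol article*

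**What the plan says.** Under Aims, the first aim has an ordered set of steps. The fixed threshold comes first: "We will therefore assess the concordance of patient classification using this MPR <2.0 threshold against endotypes determined by invasive testing". The data-derived value follows: "we will assess the MPR value with the highest area under the curve (AUC) for classification of microvascular angina based on the invasive tests". The Sample size calculation section returns to it: "We will further assess the MPR ratio with the highest AUC for microvascular angina classified invasively". No other criterion for choosing the cut-off is given in either place.

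The primary outcome does not depend on the derived value. It is stated as: "Abnormal myocardial perfusion reserve (global MPR <2.0").

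On the source of patients, the Participants section says: "Only patients randomised in the CorMicA trial (both in the intervention and control groups) are eligible to participate in the CorCMR substudy". The parent trial plans to randomise 150. No second cohort is described. The Statistical analyses section refers statistical matters to a separate analysis plan that covers this substudy and is not shown here.

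**The concern.** There are two linked issues.

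The first is the criterion. AUC is ordinarily one number for the whole ROC curve of continuous MPR, so it does not rank cut-offs along that curve. A reader cannot tell whether the product is a ROC AUC, a Youden-type cut-off, or a comparison of several MPR summaries (the outcomes box lists both global and segmental MPR).

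The second is optimism. If the cut-off is chosen because it gives the best agreement with the invasive classification, the quantity being maximised is itself an accuracy estimate from the selection sample. Quoted as it stands, it favours the test.

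This matters because the article says that no threshold for abnormal MPR is accepted and gives validation of diagnostic accuracy as a purpose of the substudy. A cut-off derived here is likely to be picked up by readers, and both its accuracy and its precision could be overrated.

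**Working it through.** **1. What the phrase can mean.** For MPR dichotomised at one cut-off, the ROC curve has a single interior point, and the area under it is

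AUC = (Se + Sp)/2 = (1 + J)/2, where J = Se + Sp − 1 is Youden's index.

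A numerical check on simulated data gave 0.5916 for both the rank-based AUC of the dichotomised test and (Se + Sp)/2. Choosing the cut-off with the highest AUC is therefore the same as maximising J. That is a workable rule, but the article does not name it.

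**2. The stated sample sizes and what they size.** The main scenario in the article is that "a sample size of 110 subjects would enable a minimum clinically significant correlation of 0.3 to be detected with 90% power at a 5% significance". The article then adds a fallback scenario for the case of fewer usable scans: "If only 60 subjects have available data, then 80% power would be available to detect a correlation of 0.37 at the 5% level". With Fisher's z, two-sided 5% (sidedness is not stated), N = ((z_α + z_power)/atanh r)² + 3:

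- r = 0.30, 90% power: ((1.960 + 1.282)/0.3095)² + 3 = 112.7, so 113. Power at N = 110 is 89.3%. The figure reproduces closely.
- r = 0.37, 80% power: ((1.960 + 0.842)/0.3884)² + 3 = 55.0, about 56 after rounding up. Power at N = 60 is 83.5%, so the fallback is slightly conservative.

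Both figures size the correlation between CFR and MPR. Neither is a stated sample for the ROC analysis, so the check below uses 60, 110 and the ceiling of 150 (the whole parent trial).

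**3. Size of the optimism.** Inputs not in the article are assumed: MPR normal with equal variance in patients with and without microvascular angina, true AUC 0.66 to 0.80, prevalence 30% to 70%. In each of 10,000 simulated studies per scenario, the cut-off maximising J was chosen in the sample. Its apparent J was compared with the true J of that same cut-off. Because (Se + Sp)/2 = (1 + J)/2, an excess in J is halved to give the excess in the mean of sensitivity and specificity.

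| n | Example (AUC 0.70, prevalence 50%): apparent J vs true J | Excess in J over all scenarios | Excess in mean of Se and Sp |
|---|---|---|---|
| 60 | 0.39 vs 0.26 | 0.11 to 0.14 | about 5 to 7 points |
| 110 | 0.36 vs 0.27 | 0.07 to 0.10 | about 4 to 5 points |
| 150 | 0.35 vs 0.27 | 0.06 to 0.09 | about 3 to 4 points |

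The chosen cut-off is also unstable. In the example scenario its standard deviation across studies is 0.47 within-group MPR standard deviations at n = 60, 0.39 at n = 110 and 0.36 at n = 150.

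**4. What is not biased.** In the same kind of simulation (true AUC 0.70, n = 60 and 110), the AUC of continuous MPR averaged 0.70, and J at a fixed cut-off averaged 0.29 against a true value of 0.29. The optimism comes only from choosing the cut-off and judging it in the same patients.

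**The case against.** The strongest reply has four parts.

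- **The phrase is not meaningless.** A reader might infer that a cut-off has no AUC at all. Step 1 of the working shows otherwise, so the defect is a loose criterion that needs naming.
- **Inflated reporting is not stated.** A reader might infer that the study will publish uncorrected accuracy at the derived cut-off as a validated result in 60 to 110 patients. The article does not say so. It says only that the value will be assessed. The second aim and the diagnostic accuracy entry in the outcomes box do not name the derived cut-off, and the validation language concerns quantitative perfusion CMR in general. Internal validation is commonly left to the analysis plan, which is not shown, so its absence from the article is not a fault.
- **The main results do not depend on it.** The fixed threshold is assessed first and defines the primary outcome.
- **The bias is modest beside the sampling error.** With 55 patients per class and Se = Sp = 0.65, the standard error of (Se + Sp)/2 is ½ × √(2 × 0.65 × 0.35/55) = 0.045. That is 4.5 points, about the same as the bias at n = 110.

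All four stand, and they limit the point to a conditional one about a secondary analysis. They do not remove it. The loose criterion is in the article's own text, in two places. The design offers one cohort, and the optimism persists even if all 150 parent-trial patients are scanned. Unlike sampling error, it always runs in the test's favour, and an ordinary confidence interval does not show it.

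**Conclusion.** The point holds as a low-cost improvement. The rule for the derived cut-off should be named, and accuracy at that cut-off would be optimistic if quoted uncorrected from the same patients. The size is about 3 to 7 points in the mean of sensitivity and specificity for 60 to 150 patients. That rests on a binormal model, an assumed AUC of 0.66 to 0.80 and an assumed prevalence of 30% to 70%.

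The documents do not support the stronger conclusion that the study's reported accuracy will be inflated. Same-sample reporting without correction is an inference from there being a single cohort, and the analysis plan may already deal with it. The primary outcome, the concordance at MPR below 2.0, the AUC of continuous MPR and the correlation sample size are all unaffected.

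**What to change.** Reword the sentence in Aims and its repeat under Sample size calculation so that they say the following:

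1. The AUC of continuous MPR for invasively classified microvascular angina is reported with a 95% confidence interval, as the threshold-free measure.
2. A cut-off is selected by Youden's index and labelled exploratory.
3. Its sensitivity and specificity are given after bootstrap optimism correction, with the cut-off re-selected in every resample, together with a bootstrap confidence interval for the cut-off itself.
4. The main accuracy statement stays on the prespecified MPR below 2.0.

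If the analysis plan already contains the correction, only the wording of the two sentences needs to change. Otherwise the cost is a short extra analysis on data already collected and a slightly less favourable reported accuracy. No extra patients are needed.

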
### Statistical analyses

The CorMicA trial has a comprehensive statistical analysis plan that governs all statistical aspects of the study authored by the trial statistician. The statistical analysis plan includes the prespecified CorCMR substudy that is designed to assess for associations between CMR measures and invasive measures and endotypes (reference dataset). Continuous outcomes will be analysed using linear regression with adjustment for baseline levels where available. Where continuous data are clearly not normally distributed, standard transformations will be applied to achieve approximate normality prior to analysis. Appropriate alternative regression methods will be applied to other types of data (eg, logistic regression for binary outcomes).

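### Associations of perfusion with baseline characteristics and baseline CMR data are worded against abnormal perfusion, and global MPR is listed only as yes/no at a cut the article calls unaccepted; continuous MPR should lead

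*Protocol article*

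**What the plan says.** All references are to the protocol article.

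- **Aims.** One aim is to assess "The associations between baseline patient characteristics and abnormal myocardial perfusion". Another relates abnormal tissue characterisation to abnormal perfusion. On the cut itself the section says "There is no accepted threshold for abnormal MPR". It takes 2.0 because that value is commonly used for invasive CFR, where cuts from 1.5 to 2.6 have been described. It also plans to look for the MPR value with the highest AUC. Reduced stress MBF, the endocardial:epicardial ratio and the dyssynchrony index are named as further abnormal metrics, without cuts.
- **Primary outcome.** "Abnormal myocardial perfusion reserve (global MPR <2.0", a binary variable.
- **Secondary outcomes box.** Global MPR appears only as a yes/no item at 2.0. Segmental MPR and stress and rest MBF carry no cut. Three association families are headed in terms of abnormal perfusion: with baseline characteristics, with invasive test data and with baseline CMR data. Only an item under the invasive-test heading is marked as both continuous and binary.
- **Statistical analyses.** Linear regression is planned for continuous outcomes, after transformation where they are clearly not normal, and "logistic regression for binary outcomes". The section refers to a statistical analysis plan that is not shown.
- **Sample size calculation.** MPR is treated as continuous, in a correlation with CFR, where the article names a "minimum clinically significant correlation of 0.3" and gives 110 subjects for it. The stated power is 90% and the level is 5%.

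**The concern.** Taken together, these sections point to logistic regression on MPR below 2.0 for two families of associations: sex, age, risk factors, risk scores and Gensini score in one; LV volumes and mass, strain, T1, ECV and LGE in the other. The outcome would be a measured quantity reduced to two classes at a value that the article itself treats as provisional.

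Two things would be at stake. Dichotomising discards information, so real associations are more easily missed. The results would also be tied to the chosen cut: a patient at 1.95 and one at 2.05 count as opposites, while one at 1.2 and one at 1.95 count as the same. If the AUC analysis favours another value, every such association would have to be refitted. Continuous MPR avoids both problems, and it must be available, because the sample size rests on it.

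**Working it through.** **Inputs.** N = 110, r = 0.30, 90% power and 5% level, from the sample size calculation. Sidedness is not stated; two-sided is assumed. The article does not give the proportion p of patients below 2.0, so it is varied. r and N belong to the CFR–MPR correlation and are borrowed here to put a size on the loss.

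**Step 1: reproduce the plan's own figure (both variables continuous).** By Fisher's z, N = ((z₀.₉₇₅ + z_power)/atanh(r))² + 3.
- r = 0.30, 90%: ((1.960 + 1.282)/0.3095)² + 3 = 112.7, so 113 against the stated 110.
- Power at 110 = Φ(0.3095·√107 − 1.960) = Φ(1.242) = 89.3%. The stated figure reproduces to within 3 patients and 0.7 points.
- The fallback statement, "If only 60 subjects have available data, then 80% power would be available to detect a correlation of 0.37 at the 5% level", comes out at 83.5% by the same formula (56 patients suffice for 80%), so it is conservative. A noncentral t with noncentrality r√N gives 80.5%.

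**Step 2: cut MPR at 2.0.** Under bivariate normality the correlation with the yes/no variable is r_pb = r·φ(c)/√(p(1−p)), with c = Φ⁻¹(p). It goes into the same power formula. For p = 0.5: r_pb = 0.30 × 0.399/0.5 = 0.239, and power = Φ(0.2441·√107 − 1.960) = Φ(0.565) = 71.4%.

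N = 110, r = 0.30, continuous power 89.3%:

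| Below 2.0 | r_pb | Power with cut | Loss (points) | Relative efficiency |
|---|---|---|---|---|
| 50% | 0.239 | 71.4% | 18 | 0.64 |
| 40% or 60% | 0.237 | 70.4% | 19 | 0.62 |
| 30% or 70% | 0.228 | 66.9% | 22 | 0.58 |
| 20% | 0.210 | 59.7% | 30 | 0.49 |
| 10% | 0.175 | 45.0% | 44 | 0.34 |

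At a median split, 110 × 0.64 ≈ 70: the dichotomised data carry the information of about 70 patients.

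**Step 3: other sample sizes.**

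| N, r | Continuous | Cut, 50% below | Cut, 30% below |
|---|---|---|---|
| 60, 0.37 | 83.5% | 63.2% | 58.6% |
| 60, 0.30 | 64.7% | 45.3% | 41.7% |
| 150, 0.30 | 96.3% | 84.1% | 80.2% |

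The smallest loss in these tables is 12 points (N = 150, half below).

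**Step 4: check by simulation, N = 110, r = 0.30.** With 20,000 runs and a t-test on the correlation, power is 89.4% continuous, 71.8% with half below and 67.7% with 30% below. With 2,000 runs of a logistic likelihood-ratio test it is 72.4% and 70.4%, a loss of 17 and 19 points against 89.4%. The size of the loss does not hinge on the approximation.

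**The case against.** The strongest reply is that the article never says what the criticism needs it to say. The aim and the box headings name no metric, cut or model. Other perfusion metrics are also called abnormal, and the box item that simply records perfusion as abnormal or not is the visual read, not MPR. The heading over the invasive-test family uses the same term and yet contains an item on both scales, so abnormal perfusion may be loose shorthand. Segmental MPR and global stress and rest MBF are listed without cuts, linear regression is already provided for, and the outcome scale in secondary models may be settled in the unseen analysis plan. The article is also open about the status of the cut.

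Much of this stands. A reader might infer that the plan states that these associations use MPR cut at 2.0; it does not. A reader might also take a loss of about 20 points as a property of the plan; it is conditional on borrowed inputs and an assumed split. Nor can unstable logistic models be claimed, since no multivariable model with a given set of factors is described.

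What the reply does not remove is that the outcome list, which the article does give, has global MPR only as yes/no, that 2.0 on global MPR is the only numerical definition of abnormal quantitative perfusion, and that these two families carry no provision for a continuous scale.

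**Conclusion.** The point holds as a matter of wording with a statistical consequence. Binary MPR is the natural reading for the baseline-characteristic and CMR-data associations, though not an explicit commitment. If the cut alone is used, power at n=110 and r=0.30 falls from about 89% to about 67–71% with 30–70% of patients below 2.0. It falls further with a more extreme split (45% with one patient in ten below), while the loss is about 12 points at n=150 with half below. This assumes bivariate normality, a two-sided 5% test of one factor at a time, and r and N taken from a calculation made for another question.

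The analyses concerned are secondary and exploratory. It would be wrong to infer that the primary outcome or the sample size is undermined: the primary is a proportion at a declared cut, and the 110 reproduces for the correlation it was meant for.

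**What to change.** In the outcome list, add global MPR as a continuous variable, transformed if skewed. For the associations with baseline characteristics and with baseline CMR data, state that linear regression on continuous global MPR is the main analysis and that logistic regression on MPR below 2.0 is supportive. If the statistical analysis plan already says this, bring the article's outcome list and headings into line with it. Leave the primary proportion, the concordance analysis at 2.0 and the sample size as they are.

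The cost is wording only: no new data, patients or methods, since linear regression with transformation is already in the statistical section. The downside is that results are expressed per unit of MPR (or on a transformed scale), which is slightly less direct for clinicians than yes/no. Reporting the supportive yes/no models alongside covers that.
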